### Biological samples

#### Sample collection

Biological samples will be collected at each participating site following agreed protocols and guidance from the central biospecimen coordination centre (Oxford BRAIN MATRIX Laboratory). The aim is to build as much as possible on existing GEL infrastructure and pathways. The funded pathway is represented in figure 3.

**Figure 3 F3:**
[figure not shown]
Sample and data flow pathways within the Tessa Jowell BRAIN MATRIX Platform (TJBM) study. *TJBM sites in England are encouraged to route all samples through their local NHS GMS GLH; however, if this pathway is not yet activated or GEL consent cannot be obtained, the TJBM Study Office can facilitate the processing of samples through an alternative NHS GMS GLH or via the GEL Research pathway. GEL, Genomics England; GLH, Genomic Laboratory Hub; GMS, Genomic Medicine Service; GTAB, Genomics Tumour Advisory Board; NHS, National Health Service; WGS, whole-genome sequencing.

Fresh tissue for TJBM must be frozen in liquid nitrogen and stored until shipment to the Oxford BRAIN MATRIX Laboratory. Matched ‘germline’ DNA from white blood cells is required for the detection of somatic variants for paired blood/tumour WGS. This should be collected as per standard GEL protocols. Ideally, it should be collected prior to or at the time of first surgery. The blood sample(s) must be shipped together with the frozen tissue of the patient to the Oxford BRAIN MATRIX Laboratory.

For patients who are not undergoing surgery and have available tumour samples from previous tumour surgery, blood should be collected and sent to the Oxford BRAIN MATRIX Laboratory along with their tumour samples.

For participants unable to donate a blood sample, a saliva sample is an acceptable alternative.

Where possible, it is intended to collect blood samples for liquid biopsies of the tumour (eg, tracking circulating tumour cell free (cft)DNA within the blood). Samples should ideally be collected at the time of operation, before the neurosurgeon performs any incision, ideally in theatres or the anaesthetics room just before any biopsy. Where feasible, further blood samples should be collected at the following key treatment milestones:

At first postoperative MRIInitiation of concomitant therapy (if applicable).The end of concomitant therapy (if applicable).Initiation of adjuvant therapy (if applicable).The end of adjuvant therapy (if applicable).The time of objectively measured progression.During the palliative phase if a post mortem has been agreed.

Where cerebrospinal fluid (CSF) is available for the patient, this should also be submitted.

Participating sites should follow the CRUK PEACE study protocol for postmortem neurological tissue donation. The aim of postmortem tissue donation is to enable research into:

The clonal evolution of the glioma after emergence of therapy resistance.Tumour–host interaction at the whole brain level.The effect of radio-chemotherapy on normal brain.The interaction between the glioma and non-CNS organs (eg, immune system in the cervical lymph nodes).

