## Introduction

Gliomas are the most common primary tumour of the central nervous system (CNS), with an estimated annual incidence of 6.6 per 100 000 individuals in the USA,^1^ which is predicted to rise to 22/100 000 by 2035.^2^ In 2016, there were 5250 deaths from brain tumours in the UK, that is, 14 deaths per day.^2^ Malignant CNS tumours hold the poorest prognosis and are responsible for the highest estimated number of years of potential life lost (mean 20 years) among all cancers,^3^ and survival trends have remained generally static in comparison with other cancers.^4^

Gliomas have traditionally been divided into low-grade glioma (LGG; WHO I–II) and high-grade glioma (HGG; WHO III–IV) based on integrated classic histological features and molecular biomarkers.^5^ LGGs have an indolent course with patients commonly surviving a decade after diagnosis.^6^ However, the natural history of many WHO Grade II LGGs is progression to HGG. Approximately half of all newly diagnosed gliomas are classified as glioblastoma (GB; WHO IV), the most malignant type of brain cancer. Currently, the GB annual incidence is 3.2 per 100 000 population in the USA. This tumour occurs more frequently with advancing age; ranging from 0.4 per 100 000 population aged 20–34 years to over 15 per 100 000 population aged 75–84 years.^1^ It is widely recognised that elderly populations are rapidly increasing globally and this will have a significant impact on the burden of GB disease. Despite this, most studies still focus on patients younger than 65 years.

The current gold-standard treatment for newly diagnosed GB is surgical gross total resection, followed by radiotherapy with concomitant and adjuvant temozolomide. The aim of treatment is to delay tumour progression and extend overall survival.^7^ Despite decades of refinement, this approach results in a median survival time of only 12–14 months.

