### Patient selection

Patients aged ≥16 years with newly diagnosed suspected WHO Grade II–IV glioma (as evidenced radiologically) suitable for a diagnostic or therapeutic surgical procedure resulting in a tumour sample matched to a blood sample or with progression with known WHO Grade II–IV glioma will be eligible.

Patients with primary spinal cord tumours, who are receiving active treatment of other malignancy, have contraindications to MRI and/or without standard of care imaging available, will be excluded.

Newly diagnosed patients with suspected WHO Grade II–IV glioma who are subsequently found to have a WHO Grade I tumour or non-brain tumour are expected to be a rare occurrence. If this event occurs:

If it is confirmed as a Grade I tumour, then the patient will remain eligible for the study and will continue to be followed up in accordance with the protocol.If it is confirmed as a non-brain tumour, then the patient will not remain on the study and no further follow-up data will be collected.

All patients must be able to provide written informed consent for the study.

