OS is defined as the time from date of diagnosis to the date of death with patients who are alive at the time of analysis censored at the date last seen in clinic. Intracranial PFS time is defined as the time from date of registration to the earliest of date of intracranial progressive disease or death from disease. The date of an event is defined as the earliest confirmation of progression by radiological assessment, clinical symptoms or multidisciplinary team (MDT). Patients without progression at the time of analysis will be censored at the date last seen in clinic.

OS and intracranial PFS will be analysed and plotted using the Kaplan-Meier method. Median times with corresponding 95% CI will be reported together with rates at 1, 2 and 5 years. Multivariable survival regression modelling will be used to explore prognostic factors, including, but not limited to, WHO 2021 classification, age, tumour volume, stage, methylation and mutation status.

Longitudinal measures of QoL will be generated from the QoL questionnaire according to the questionnaire-specific algorithms for scoring. The analysis of longitudinal QoL scores will essentially be descriptive. For each of the multiple QoL scores generated from the different questionnaires, the means, medians or proportions (as appropriate) will be plotted over time together with 95% CI. These repeated measures over time may be modelled, if appropriate, with a linear or more flexible mixed model that takes account of the within-subject correlation and will allow exploration of factors associated with the outcome.

Details of the type of intervention received and complications (eg, surgical wound infection) relating to SoC treatments received will be monitored and recorded throughout the follow-up period and reported descriptively as frequencies and associated percentages. In relation to initial local logical diagnosis, local pathological diagnosis and integrated histological–molecular diagnosis, any difference between the tiers of diagnoses will be highlighted and categorised as discordant, agreed, refined and reported descriptively as frequencies and associated percentages.

Confirmation of central storage of images and material, relevant targetable mutations identified by WGS and EC, and receipt of postmortem consent forms with confirmed central storage of samples will be recorded and reported descriptively.

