## Discussion

### Justification for patient population

The main aim of the TJBM study is to test the hypothesis that comprehensive genomic and epigenomic profiling of gliomas is feasible in a timely manner in the UK, and that the results improve stratification of patients for next-generation (targeted) therapies, ultimately improving outcomes and QoL.

Gliomas occur at all ages and their specific subtype is difficult to predict preoperatively. Therefore, the patient population eligible for the TJBM study is broad. It includes any patient who on preoperative assessment is suspected to have a diffuse glioma, or where a diffuse glioma remains a credible differential diagnosis, as established by the MDT at the recruiting site.

Recruitment is also open to patients with diffuse or atypical gliomas who had a biopsy before the launch of the TJBM study. This approach ensures that:

Patients with slow-growing diffuse gliomas that evolve over many years (oligodendrogliomas) may benefit from one or more of the clinical trials developed as part of the TJBM study and sample collection at tumour progression.Patients who potentially benefit most from comprehensive molecular diagnostics are not missed, which often are those with rare or atypical variants of glioma based on current diagnostics.^34^

The infrastructure for children with brain tumours in the UK is different to that of adults with epigenomic classification regularly used and with WGS shortly to be made available for all children with cancer. Thus, the challenges and opportunities are different for paediatric patients. Nevertheless, it is intended that children will be included within the TJBM study wherever appropriate. The recruitment of children and adolescents into the TJBM study will be coordinated with the UK’s paediatric oncology expert group(s).

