### Justification for tissue collection

Historical approaches to brain tumour tissue collection in formaldehyde and paraffin are not currently fully compatible with modern genomic technologies, which require frozen tissue. This is why the collection of fresh frozen material is essential for the TJBM study. Pairing with non-neoplastic, so-called germline DNA is also essential for confident calling of somatic variants in the tumour. Germline DNA analysis will also provide novel data on genetic risk for glioma predisposition.

Blood plasma, where possible, will be collected to facilitate future analysis of cftDNA. This technology is still in its infancy; however, it is clear that non-invasive, real-time monitoring of tumour evolution will become feasible in the next 5–10 years.^35^ Similarly, where available for the patient, CSF will be submitted.

Postmortem tissue banking via the CRUK PEACE and MRC Brain BioLink projects will allow us to study the glioma–brain interface, extent of spatial tumour heterogeneity, genomic signature of the treatment resistant tumour clones and effect of treatments on normal brain. Systematic postmortem brain banking for research into adult gliomas does not currently exist in the UK.

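### Intracranial PFS runs from registration for newly diagnosed and progression entrants together, entry route is neither a named factor nor a subgroup, and unoperated progression entrants are typed on earlier tissue

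*Protocol article*

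**What the plan says.** All references are to the protocol article.

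- **Entry routes.** Patient selection admits newly diagnosed suspected glioma and also patients "or with progression with known WHO Grade II–IV glioma will be eligible". Justification for patient population adds: "Recruitment is also open to patients with diffuse or atypical gliomas who had a biopsy before the launch of the TJBM study". One reason given there is that patients with slow-growing tumours "may benefit from one or more of the clinical trials developed as part of the TJBM study and sample collection at tumour progression".
- **Tissue.** Biological samples, Sample collection (text after Figure 3): "For patients who are not undergoing surgery and have available tumour samples from previous tumour surgery, blood should be collected". The blood goes to the central laboratory together with the earlier tumour samples. No limit on the age of the tissue is given.
- **Clock.** Statistical analysis plan: "Intracranial PFS time is defined as the time from date of registration". One origin serves every patient. Overall survival runs from diagnosis instead.
- **Use of the typing.** The same section names WHO 2021 class, methylation and mutation status among the factors for multivariable survival models. IDH and methylation status also define planned subgroups. Neither list contains newly diagnosed versus progression entry.
- **Change over time.** The Introduction states that "the natural history of many WHO Grade II LGGs is progression to HGG". Among the research aims for post-mortem tissue is "The clonal evolution of the glioma after emergence of therapy resistance".

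**The concern.** PFS from registration means one thing for a patient about to start first-line treatment and another for a patient whose tumour has already progressed. A single Kaplan-Meier curve over both describes a mixture. Its medians and its 1-, 2- and 5-year rates depend on how many of each kind happened to be recruited.

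The molecular associations inherit the problem. If progression entrants are more common in one tumour class than another, part of the apparent difference between classes is a difference in entry route. The stated reason for admitting previously biopsied patients, access for slow-growing tumours, suggests that the shares may indeed differ by class.

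A second, narrower problem concerns progression entrants who have no new operation. Their class is read from tissue that predates registration, while the outcome clock starts at registration. If the tumour has changed grade in between, the covariate describes an earlier state. The article's stated aim is to improve stratification of patients, and these analyses bear directly on it.

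**Working it through.** The plan offers no figure to reproduce. The target of 1000 is stated to have no statistical basis, and the article gives neither the share entering at progression, nor the share typed only on earlier tissue, nor the share whose class has changed. The check is therefore a side-by-side reading, followed by arithmetic on declared assumptions.

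**Reading the sections together**

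1. Patient selection and Justification for patient population create two entry routes.
2. The Statistical analysis plan gives both the same PFS origin, which for a progression entrant falls after a progression.
3. Sample collection sends a subset of progression entrants (no surgery, earlier sample available) to typing on earlier tissue.
4. The survival models and subgroups use that typing and name no term for entry route.

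Steps 1, 2 and 4 establish the pooling. Step 3 adds the possible age of the covariate.

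**Pooling of entry routes**

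Let s be the share entering at progression. With the two groups' PFS curves S_new and S_prog, and ignoring differences in censoring:

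S_pooled(t) = (1 − s)·S_new(t) + s·S_prog(t), so S_new(t) − S_pooled(t) = s·[S_new(t) − S_prog(t)].

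If s is assumed to lie between 10% and 50%, the pooled rate differs from the newly diagnosed rate by 10% to 50% of the gap between the groups. That is 1 to 5 percentage points for each 10 points of gap. The article does not give the gap.

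**Outdated class in unoperated progression entrants**

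All inputs are assumed:

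- s: share entering at progression
- a: share of those typed only on earlier tissue
- c: share of those whose class has since moved from lower to higher risk
- true hazard ratio between classes: 2.0

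The share of the lower-risk group carrying an outdated class is m = s·a·c. The hazard in that group is (1 − m)·1 + m·2 = 1 + m, so the observed ratio is 2/(1 + m).

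| Case | s | a | c | Typed on earlier tissue, per 1000 (1000·s·a) | m | Observed ratio |
|---|---|---|---|---|---|---|
| Low | 0.10 | 0.25 | 0.10 | 25 | 0.0025 | 2/1.0025 = 2.00 |
| Middle | 0.30 | 0.50 | 0.30 | 150 | 0.045 | 2/1.045 = 1.91 |
| High | 0.50 | 1.00 | 0.50 | 500 | 0.25 | 2/1.25 = 1.60 |

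This calculation takes the same share of progression entrants in each class and compares hazards early in follow-up. It covers the outdated class only, not the pooling of entry routes.

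**The case against.** The strongest reply is that the group typed on earlier tissue may be small. The sample rule reaches only unoperated patients with stored samples. Sample collection at progression is foreseen for others, and Justification for tissue collection, after noting the limits of older fixed tissue, says "This is why the collection of fresh frozen material is essential for the TJBM study". That stands. A reader might infer that all progression entrants are typed on old tissue, but the text does not say so. Nor are re-operated patients a fault in typing: their tissue matches the state being followed.

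Second, the documented change is in grade. A reader might infer that IDH or methylation status also goes out of date. No section says so. For those markers the supported concern is the mix of entry routes, not mistyping.

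Third, a reader might try to size the effect from the survival medians in the Introduction. Those are overall survival figures, and the shorter one is for newly diagnosed glioblastoma on standard treatment. The plan measures overall survival from diagnosis and only PFS from registration, so such a calculation would estimate neither planned endpoint.

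Fourth, the factor list is expressly open and includes an undefined stage term, the modelling is exploratory, and a full protocol or separate analysis plan may already stratify. This limits the weight of the point. It does not remove it: the article does fix a single PFS origin for everyone and does list its subgroups, and following that text pools the two routes.

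Finally, a PFS clock from registration is not wrong in itself for a progression entrant. It measures time to the next progression, and that is why it should be shown separately.

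**Conclusion.** The point holds in limited form. On the article's text, PFS summaries and the associations of PFS with WHO class, IDH and methylation status combine first-line and post-progression courses. For progression entrants without new surgery, the WHO class may in addition predate a change of grade.

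The size is unknown. For the outdated class alone, the assumed ranges run from no visible effect to a hazard ratio of 1.60 where the truth is 2.0, with 1.91 at middle values. Nothing in the article shows where in that range the study will lie. The effect of pooling depends on the share of progression entrants and on the PFS gap between the groups, neither of which is given.

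Time to integrated diagnosis, the primary outcome, is not affected by this point. PFS is secondary and no decision rule hangs on it. The change is still worth making, because analysis by entry route is clearly more interpretable than the pooled one and costs little. The article does not support the conclusion that the molecular analyses are invalid, or that patients with archived tissue must leave the main models. Exclusion is a debatable trade-off, and adjustment for entry route would keep them.

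**What to change.** 1. Report intracranial PFS (curves, medians, and 1-, 2- and 5-year rates) and targetable-mutation frequencies separately for newly diagnosed and progression entrants.
2. Stratify the PFS prognostic models by entry route, and add entry route to the planned subgroups.
3. Record the date of the source sample with each whole-genome sequencing and epigenomic result.
4. Add a sensitivity analysis of the molecular models for PFS limited to tissue taken near registration, with the time window set before the analysis.

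The cost is mainly analysis wording. Entry route follows from the eligibility criterion met, and the date of biopsy is already needed for the primary outcome. The price is smaller strata and slightly wider confidence intervals. If the full protocol or a separate analysis plan already does this, a sentence saying so is enough.

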#### Sample analyses

Matched tumour/blood samples collected at first surgery are the most important samples of the TJBM study as these determine the initial integrated histological–molecular diagnosis. Following histological QC, the Oxford BRAIN MATRIX Laboratory will perform DNA extraction and QC; an aliquot will be sent to the Illumina Centre in Cambridge for WGS and one used for EPIC methylation array at the Wellcome Trust Centre for Human Genetics in Oxford. Remaining DNA and unused tissues will be stored at the BRAIN MATRIX Biorepository.

Raw WGS data will be maintained in the GEL Data Research Environment, where it can be accessed and re-analysed by data scientists at the submitting NHS Genomic Laboratory Hub or any qualifying TJBM-approved researcher. Sample data not generated by GEL will be consolidated in established bioinformatics hubs of the University of Oxford (Big Data Institute/Weatherall Institute for Molecular Medicine).

Data files on the Illumina 850k EPIC BeadChip analysis will be uploaded to the ‘Heidelberg Classifier’ hub at the German Cancer Centre in Heidelberg.^27^ This will generate an automated classifier report which will be stored at the Oxford BRAIN MATRIX Lab. Raw array data will be made available via the Oxford BRAIN MATRIX Laboratory.

Matched histological sections will be digitised at the Oxford BRAIN MATRIX Laboratory resulting in linked genomic data, which will initially be stored in Oxford. As the study evolves, we will aim to capture digital histological data from the material kept at the local neuropathology centre. The Oxford BRAIN MATRIX hub is working with CRUK-established data visualisation platforms, such as those developed for S:CORT (Colorectal Cancer)^28^ and based on international open access platforms (such as cBioPortal^29^).

The BRAIN MATRIX neuropathology and genomics team will generate an integrated report (histology, WGS, Heidelberg Classifier) for each case in consultation with the local neuropathology team. The primary BRAIN MATRIX report will comprise the formal routine GEL WGS report (germline and tumour) and Heidelberg Classifier report and integrate this with the histological and molecular report issued by the recruiting site. It is anticipated that a local histological and molecular diagnosis using immunohistochemical surrogate markers and targeted genetic analyses will be available before WGS and Illumina EPIC BeadChip data are returned to the Oxford BRAIN MATRIX Laboratory. When available, the BRAIN MATRIX neuropathology and molecular genetics team will conduct a virtual MDT meeting with the referring site to ensure all relevant information will be incorporated in the final BRAIN MATRIX diagnostic report. Variant calling and classifier outputs will be determined by the practice at the GEL/Illumina Centre and the version of the Heidelberg Classifier algorithm active at the time of sample analysis.

Where relevant germline data are identified, local sites should facilitate local genetic referral as per other GEL study protocols.

